#### Software

Self-monitoring will be conducted on the basis of smartphone application for Android devices. A comparison of such software solutions is provided in Kubiak and Krog (42). MovisensXS will be used as a specialized software for the research methodology of AA, that has been used extensively in research studies (43). MovisensXS is designed to collect subjective self-reports of the participant in daily life and is based on the Android operating system. It consists of two components. First, a web-based portal for study administration used by the researcher. Second, a smartphone app for data collection. The application assesses self-reports throughout the day and, depending on the research question, can be triggered at random times, by the participants themselves or from context parameters.

#### Intervention

The intervention consists of two components: self-monitoring and support.

##### Self-Monitoring

During the 28-day intervention period, daily self-monitoring on the basis of AAs will be conducted. The research methodology of AA is well suited to study people in their natural environment, resulting in ecologically valid data from the persons’ everyday life (44). The self-monitoring protocol should detect and monitor micro-processes of mental health and intra-individual variability, as well as the contextual factors in daily life. We aimed to design a brief, but comprehensive protocol for daily self-monitoring of mental health based on self-reports, while attempting to keep participant burden low. The most common areas of psychopathology will be included: Mood, depression, anxiety, stress, sleep, and functional impairment. In addition, physical activity, social activity, daily hassles and daily uplifts, and alcohol and drug use will be monitored as risk and protective factors of mental health. With a total length of 23 items, participants will be able to complete a daily report in under 5 min. All AAs will be time and date stamped.

*Mood*: To self-monitor daily mood, we will use the version of the Multidimensional Mood State Questionnaire (MDBF) from Wilhelm and Schoebi (45). The MDBF was designed specifically for daily life studies with repeated mood ratings, where a parsimonious measure that is sensitive for change is needed. It uses six items to assess the three factors calmness, valence, and energetic arousal in the present moment. Responses are indicated on three separate six-point bipolar scales with the endpoints labeled “very” (“good–bad,” “awake–tired,” and “calm–nervous”).

*Depression*: depression is one of the most common mental health problems. The Patient Health Questionnaire-2 (PHQ-2) will be used to self-monitor daily depressive symptoms. The PHQ-2 uses two items to score the frequency of depressed mood and anhedonia on the present day on a 4-point scale ranging from (0) “*not at all*” to (3) “*nearly all of today*,” which results in a total score ranging from 0 to 6. The PHQ-2 was originally developed as short screening scale for depression during the past 2 weeks, and will be adapted for the present project to assess depressive symptoms on the present day (46, 47). The PHQ-2 has demonstrated good sensitivity to change and its diagnostic properties were found to be comparable to longer screening instruments. Using PHQ-2 score of 3 as cut point, the authors report that the overall diagnostic accuracy of the PHQ-2 as measured as the “Area under the curve” is 0.90 for major depressive disorder (47); however, the authors also state that a cut point of 2 would enhance sensitivity, and a cut point of 4 would improve specificity.

*Anxiety*: anxiety disorders range over a broad spectrum of experiences related to the expression of anxiety reactions and avoidance behavior. Anxiety is among the most prevalent mental disorders with 11–20% of the population affected during their lifetime. We will use the Generalized Anxiety Disorder-2 (GAD-2) as an ultra-brief monitoring scale for anxiety disorders (48). The GAD-2 uses two items to rate the presence of core anxiety symptoms. The GAD-2 showed high sensitivity for the four most common anxiety disorders: generalized anxiety disorder, panic disorder, social anxiety disorder, and posttraumatic stress disorder. While the original version references to the past two weeks, we will adapt the reference period to the present day. A cut point of 3 on the GAD-2 was reported to be optimal (48).

*Stress*: we define stress as the extent to which an individual perceives that situational demands exceed their ability to cope. To measure the extent of daily stress, we will use the 4-item version of the Perceived Stress Scale (PSS-4). The PSS-4 has two positively worded items and two negatively worded items, which correspond to a two-factor structure (49). We refer to the subscale representing the negatively stated items as “Stress” and to the subscale representing the positively stated items as “Coping.” The PSS uses a 5-point scale from 0 “*never*” to 4 “*very often*,” resulting in a total score of 0–8 for each subscale. As the PSS was not designed as a diagnostic instrument, no cut point is available.

*Daily events*: both daily hassles and daily uplifts will be monitored as risk and protective factors of mental health. Daily hassles are small, day-to-day irritations (e.g., losing things, traffic jam, arguments), while daily uplifts are small, positive events that can help reinforce a sense of well-being (50). The occurrence and appraisal of daily events will be assessed with an adapted scale from Wichers et al. (51), where respondents report the most important event of the day on a 7-point bipolar scale (−3 “very unpleasant,” 0 “neutral,” and 3 “very pleasant”). From this data, variables for positively appraised events (daily uplifts) and negatively appraised events (daily hassles) will be constructed by including the range of neutral to very pleasant events (0–3) or neutral to very unpleasant events (−3–0) events.

*Sleep*: poor sleep quality and insomnia are widespread health problems. To monitor sleeping problems, we will use a one-item measure of sleep quality extracted from the Consensus Sleep Diary, a standardized sleep scale which was designed for self-monitoring purposes (52). The item “How would you rate the quality of your sleep?” is rated on a 5-point sale from 1: very poor–5: very good.

*Physical and social activity*: as a protective factor for mental health, social activity refers to daily interactions with different groups of people in the immediate social environment. It will be measured with the item: “With whom have you spend the majority of your day?” using alone, partner, friends, family, colleagues, and other as categories. Physical activity is monitored as a protective factor of mental health and will be measured with an item extracted from the International Physical Activity Questionnaire (IPAQ SA Short) (53). The item “Have you been physically active today?” uses four answer categories to assess low-, moderate- and high-intensity activities, and also no activity as an indicator for sedentary behavior. Appropriate examples for each category will be provided for instruction (e.g., low-intensity activity “walking at least 10 min a day”).

*Alcohol and drug use*: as a risk factor for psychopathology, daily reports of drinks consumed using the categories beer, wine, liquor, and other will be collected. From this, the number of standard drinks consumed per day will be calculated. Participants will be familiarized with the concept of a standard drink and the volumes of different beverages that are equivalent to a standard drink (54). The German definition of standard drinks will be used (men: 20 g alcohol, women: 10 g alcohol). Two measures of alcohol use will be constructed: days with any drinking and days with heavy drinking (defined by five drinks for men and four drinks in for women). For drug use, the daily occurrence and frequency of any illegal substance will be assessed.

*Impairment*: the individuals’ functioning in the context of social and occupational roles, which is assumed to be a central component of mental health will be monitored. We use a single-item scale from the PHQ-4 (55), which measures subjective impairment in work and household duties and in social relationship on the present day on a 4-point scale with the item: “How difficult have these problems made it for you to do your work, take care of things at home, or get along with other people?”

*Context*: contextual information on daily locations will be monitored as a risk or protective factor of mental health. For this purpose the item “Where were you the majority of the day?” will be used with the categories: at home, visiting friends or family, work or school, outbound, and other.

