**Figure 2 F2:**
[figure not shown]
Supported self-monitoring process.

*Self-Monitoring*: participants will be able to self-monitor mental health by visual inspection of the time course for each symptom (mood, anxiety, depression, stress, sleep, impairment). This will be achieved by displaying line plots of symptom scores on the *y*-axis, and time (in days) on the *x*-axis. Participants can select the last week or the total self-monitoring period as time frame. There will be an option to display the time course of multiple symptoms simultaneously by adding or removing symptoms from the menu.*Inference of Health Status*: weekly health reports will provide text-based feedback on the user’s personal health status and symptoms. The participants’ personalized weekly health status will be derived from the mean level for each symptom during the past week. Severity categories (low, moderate, high) will be computed by using established cut points, whenever available. For example, the established PHQ-4 cut points for symptom severity of depression (47) and anxiety (48) will be used. If no cut points are available, the scales will be divided into low, moderate, and high scores according to the tertiles of the frequency distribution. The health status will also be displayed in terms of deviations from the within person-mean. Thus, the participants’ deviation of his or her mean in terms of improvements or worsening of symptoms will be displayed. As a relatively stable mean requires several days of collected data, the latter feature will be available after 1 week of use. Users will be notified whenever a new weekly health report is available with a pop-up message and an icon next to the appropriate section.*Context information*: the influence of social contexts on mental health will be displayed to the user. The context-specific health status will be displayed on a text basis, allowing the users to compare the symptoms and health in each setting. For this purpose, each of seven symptoms will be grouped by its daily context/setting. Six different contexts will be available: 1. days with daily hassles, 2. days with daily uplifts, 3. days with physical activity, 4. days with social activity, 5. days spent alone, and 6. days in company (partner or friends, family, colleagues, others). Alternatively, users may group symptoms by five different locations (1. days at home, 2. days visiting friends or family, 3. days at work or school, 4. trips/outbound, and 5. other). Thus, the user can inspect his or her mental health problems within a total range of 210 possible combination, allowing for a rich and detailed inspection of symptoms by context.*Supportive Feedback*: personalized supportive feedback will be given, based on the data collected by the participant. Feedback will presented in the form of daily health tips which can be accessed from within the application or as Android system notification. The feedback will include tips for the self-management of mental health and mental health micro-interventions (e.g., behavioral activation, problem solving, coping strategies) based on psychoeducation and cognitive–behavioral therapy (CBT) for low mood, anxiety, depression, stress, substance abuse, and sleep problems (58–60). The feedback will be adapted to the severity of each symptom within the last week (low, moderate, high). In the case of low to moderate severity, tips for the self-management of mental health and mental health micro-interventions will be displayed. Participants with moderate symptom severity will also be directed toward available evidence-based self-help programs (61, 62). In the case of severe symptoms, participants will be encouraged to seek help from a professional mental health service and will be provided with corresponding contact information on these services (e.g., hotlines, addresses, and websites of professional organizations). For each mental health problem and degree of severity, at least 10 different feedback messages will be developed, resulting in a total of at least 180 feedback messages (10 messages × 6 mental health problems × 3 degrees of severity). Additionally, a total of 40 feedback messages will be developed for the presence of daily life risk factors for mental ill-health (low social activity, low physical activity, daily hassles, and functional impairment). Users will be able to dismiss feedback messages that they do not wish to be presented again or to select feedback messages that they wish to be reminded of. All content will be developed on the basis of evidence-based guidelines or treatment manuals for the respective mental health problems (63–67).

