*Daily life data*: we will compute Cox proportional hazards models to investigate daily life behavior as risk and protective factors of mental health. Cox proportional hazards models are a type of survival model that allows for the estimation of the hazard (or risk) of an event of interest given prognostic variables. We will model changes in mental health as measured by K6 as the outcome event (i.e., improved, maintained, and deteriorated), and separate models will be computed for well-being, intentions to seek help, and help-seeking behavior as outcome event. As risk and protective factors, we will include daily life measures. Risk factors include alcohol and substance use, the frequency of daily hassles, low social activity, and low physical activity. Protective factors include coping behavior, social support, and physical activity. Furthermore, the instability or variability of daily symptoms over the 30-day monitoring period will also be examined as a risk factor by computing within-person variances, first-order autocorrelation, the mean square successive differences, and the probability of acute change according to Jahng et al. (109). Discrimination ability (the ability of the model to separate individuals who develop the event from those who do not) will be assessed with the C statistic. Model calibration, that measure how accurately model predictions match overall observed event rates, will be evaluated with a version of the goodness of fit (110). Internal model validation will be carried out. For all daily life analysis, data from the AA group will be used (*N* = 62).

*Access*: we will describe access to the intervention in terms of population characteristics (sample representativeness), demographics, clinical characteristics, and sample comorbidities using the appropriate descriptive statistics.

*Engagement*: to assess participant engagement, we will examine the proportion of study drop-outs and the proportion of enrolled individuals who respond to the outcome assessments at each time point, and the proportion of daily life assessments filled out during the 30-day interval.

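### The only daily social-activity item records the main company of the day, not the interactions that the protocol defines as social activity

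*Protocol article*

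**What the plan says.** In the Protocol article, Self-Monitoring (paragraph on physical and social activity), the construct is described as a protective factor: "social activity refers to daily interactions with different groups of people in the immediate social environment". The next sentence measures it with one question, "With whom have you spend the majority of your day", "using alone, partner, friends, family, colleagues, and other as categories".

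The variable is then used in three places:

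- **Context feedback** (Support, context information, below Figure 2). Symptoms are grouped by type of day. Three of the six listed contexts are "4. days with social activity, 5. days spent alone, and 6. days in company (partner or friends, family, colleagues, others".
- **Supportive feedback** (same section). Low social activity is one of four daily risk factors for which 40 messages in total will be written.
- **Cox models** (Statistical Analysis, daily life data). "low social activity" is listed among the risk factors. These analyses use the AA group only, N = 62.

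**The concern.** The definition is about whether interactions take place and with which groups. The item asks who dominated the day. A participant who is alone for most of the day but spends a substantial evening with friends can only answer 'alone'. A participant who meets colleagues, family and friends on one day appears to be recorded under one of them.

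If so, an association between low social activity and K6 change would be an association with predominant company, which depends in part on whom a person lives and works with. In the app, a user with real contact on mostly solitary days might receive messages meant for people with little contact. Contact that was never recorded cannot be recovered by any later coding rule.

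**Working it through.** The plan states no figure on this point that could be reproduced. The check sets the passages side by side and adds two small calculations.

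**1. Does another measure record shorter contact?**

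- The location item in Self-Monitoring also asks about the dominant setting: "Where were you the majority of the day". It has a category for visiting friends or family, but a short visit would not be the answer.
- The Oslo scale (Other Assessments, social support) measures available support, not daily contact.
- By contrast, the physical-activity item in the same paragraph asks whether activity occurred. Its example of low intensity is a walk of at least 10 minutes. Social contact of that length leaves no trace.

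**2. Could a second social item lie within the stated length?** The article says "With a total length of 23 items, participants will be able to complete a daily report in under 5 min". Counting the items described:

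| Domain | Items |
|---|---|
| Mood (MDBF) | 6 |
| Depression (PHQ-2) | 2 |
| Anxiety (GAD-2) | 2 |
| Stress (PSS-4) | 4 |
| Daily event, sleep, social, physical, impairment, location (1 each) | 6 |
| Subtotal | 20 |

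The number of alcohol and drug items is not given, so both are assumptions:

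- 1 alcohol item and 1 to 2 drug items: 20 + 1 + 1 = 22, or 20 + 1 + 2 = 23.
- 4 alcohol items (one per beverage category) and 1 to 2 drug items: 20 + 4 + 1 = 25, or 20 + 4 + 2 = 26, above the stated 23.

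At most 23 − 22 = 1 undescribed item fits, and none is described for social contact.

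**3. How much contact can an 'alone' day contain?** Read majority as more than half of waking time, w hours. An answer of 'alone' then requires more than w/2 hours alone, so contact is below w/2.

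| Waking hours w (assumed) | Contact compatible with 'alone' |
|---|---|
| 14 | just under 7 h |
| 16 | just under 8 h |
| 18 | just under 9 h |

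As an invented example, nine hours working alone and four evening hours with friends gives 'alone' whenever w/2 < 9, that is, on any waking day under 18 hours.

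**4. Can one item supply the three company-related contexts?** Two codings show what is open:

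- If every answer other than 'alone' counts as social, days with social activity and days in company are the same days.
- If, for example, colleagues and others are not counted as social, the first set is a subset of the second and the two differ.

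The article gives neither rule. Under both, contact below the majority threshold is missing from the social-activity days.

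**The case against.** The strongest reply is that an article commonly leaves variable derivation to a fuller document, so the absence of a coding rule is not a fault. That stands, and it rules out several stronger readings that a reader might infer:

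- **A day mostly alone counts as no social activity.** No section says which answers count as social activity or as low social activity.
- **Days with social activity and days in company are identical, so only four of the six contexts are distinct.** Working step 4 shows a coding that separates them. The count is also inconsistent: hassles and uplifts come from a single event item too, yet would be counted as two. Showing alone and in-company days next to each other is the comparison the user is meant to see.
- **The variable measures living and working arrangements instead of social activity.** The answer can change from day to day and it separates partner, friends, family and colleagues. The documents hold no data showing that it reflects only household and job.

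Brevity is also a declared aim, and several other domains are single items. This explains having one item, but not why that item asks about something other than the stated construct.

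A last objection concerns the remedy. If any ticked category made a social day, people who live with a partner or work in an office could tick one every day. The binary might sit near its ceiling and stay mixed with household and job. That is correct, and it is why the number of groups should be used and not only any versus none.

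The mismatch itself is untouched by these replies. The article fixes both the item wording and the response categories, so it is not a detail left for later.

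**Conclusion.** The point holds as a mismatch between construct and item. The daily question measures predominant company. It does not record shorter contact, and it appears to reduce several groups to one, subject to whether multiple answers are allowed. Low social activity is therefore a coarse measure, likely mixed with household and work setting; the documents do not support saying more than that.

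A day answered 'alone' may hold up to just under 7 to 9 hours of contact, assuming 14 to 18 waking hours and majority meaning more than half. How often such days would occur cannot be determined from the documents.

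The reach is small: one risk factor in a secondary daily-life analysis of 62 participants, who receive no feedback, and one of four risk-factor topics in the feedback given to the intervention group, where messages can be dismissed. The primary K6 comparison between groups is unaffected. This is a cheap improvement, not a threat to the trial's main conclusion.

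**What to change.** Trial Status places the trial in preparation, so the item can still be changed before data collection.

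1. Ask with whom the participant had contact that day, on the same categories, with tick all that apply and an option for nobody.
2. Use the number of groups ticked as the extent of social activity, not only any contact versus none.
3. If the alone and in-company contexts are wanted, keep the majority-of-day item for those only.
4. State which answers define each feedback context and which define low social activity.

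If the item is left as it is, rename the variable *predominant company* in the feedback description and in the Cox analysis, and limit the conclusions to that.

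**Cost:** a changed response format if the new item replaces the old one, or one added item on the 23-item daily report if both are kept. The number of groups still says nothing about the duration or quality of contact, and part of the mixing with household and work setting will remain.

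### The heavy-drinking-day indicator adjusts for sex twice, in the drink unit and again in the threshold, so the cut is 100 g for men and 40 g for women

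*Protocol article*

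**What the plan says.** The definitions stand together in the Self-Monitoring section, in the paragraph on alcohol and drug use.

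- Participants report daily what they drank, by beverage type (beer, wine, liquor, other). The reports are then converted: "From this, the number of standard drinks consumed per day will be calculated".
- The unit of conversion differs by sex: "The German definition of standard drinks will be used (men: 20 g alcohol, women: 10 g alcohol").
- Two variables are derived: "Two measures of alcohol use will be constructed: days with any drinking and days with heavy drinking". The second is "defined by five drinks for men and four drinks in for women".

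The Statistical Analysis section, under Daily life data, uses alcohol as a predictor in Cox models: "Risk factors include alcohol and substance use, the frequency of daily hassles, low social activity, and low physical activity". These models use only the group that self-monitors without support, with N = 62. No sex-specific model is described there. Gender is named elsewhere in that section only as a moderator of the intervention effect.

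**The concern.** There are two ordinary ways to build a sex difference into a heavy-drinking measure. One is to keep a single drink size and set a different number of drinks for each sex. The other is to keep a single number of drinks and let the drink size differ. The article does both. The two adjustments multiply, and the result is never written in grams, so a reader of the paragraph would not easily see how far apart the two cuts lie.

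What is at stake is the meaning of one predictor. A heavy-drinking day for a man and one for a woman are given the same value and the same regression coefficient, although they stand for very different amounts of alcohol. A coefficient for that predictor would be hard to interpret in either sex.

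**Working it through.** The article gives no gram figure for a heavy-drinking day, so there is no stated result to reproduce. The check is direct arithmetic.

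**Inputs**, all from the alcohol paragraph in Self-Monitoring:
- unit: 20 g (men), 10 g (women)
- threshold: 5 drinks (men), 4 drinks (women)

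**Cut in grams** = grams per drink × number of drinks.
- Men: 20 × 5 = 100 g
- Women: 10 × 4 = 40 g
- Ratio: 100 / 40 = 2.5

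**Where the ratio comes from.**
- Unit: 20 / 10 = 2.0
- Threshold: 5 / 4 = 1.25
- Product: 2.0 × 1.25 = 2.5

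**How given intakes are classified under the rule as written.**

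| Intake | Drinks, man | Heavy day? | Drinks, woman | Heavy day? |
|---|---|---|---|---|
| 40 g | 2.0 | no | 4.0 | yes |
| 60 g | 3.0 | no | 6.0 | yes |
| 80 g | 4.0 | no | 8.0 | yes |
| 100 g | 5.0 | yes | 10.0 | yes |

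Every intake from 40 g to just under 100 g is heavy for a woman and not for a man.

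**Same five/four rule with one common unit u.** The cuts are 5u and 4u, and the ratio is 1.25 whatever u is. The article gives no common unit, so these values are illustrations only:
- u = 10 g: 50 g and 40 g
- u = 12 g: 60 g and 48 g
- u = 20 g: 100 g and 80 g

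**Sensitivity to the wording of the cut.** If the threshold means more than five or four whole drinks, the first qualifying counts are six and five. The cuts are then 6 × 20 = 120 g and 5 × 10 = 50 g, a ratio of 120 / 50 = 2.4. The conclusion does not change.

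**Who is affected.** The sample description sets quotas of 49.8% male and 50.2% female. If those shares hold within the arm, 62 × 0.498 = 30.9 and 62 × 0.502 = 31.1, so about 31 men and 31 women. Neither sex is a small minority in the daily-life analysis.

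**The case against.** The other side has several good points.

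**A sex-specific cut is meant to treat equal intakes differently.** This stands. Even after repair, with u = 10 g, a man at 45 g is not heavy and a woman at 45 g is. Unequal classification alone is therefore no error. What remains is that the difference is applied at two steps, which takes the ratio from 1.25 to 2.5 with no reason given.

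**The threshold says drinks, not standard drinks.** This is true, and the 100 g and 40 g figures depend on reading them as standard drinks. The paragraph defines no other unit, and the conversion to standard drinks comes directly before the threshold, so this is the likelier reading. If raw beverages were meant, the text would need to say so.

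**Reach.** A reader might infer that the whole alcohol risk factor is not comparable between the sexes. The article does not support that. It constructs two measures, and days with any drinking does not depend on the unit. A reader might also infer that the twofold difference in the drink count distorts a model. The count is an intermediate step and is not named as a model variable.

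**Confounding.** A reader might infer that the alcohol coefficient is confounded with sex. The article lists risk and protective factors but not the full covariate set, and a condensed article may leave that to the full plan. Sex may be a covariate. Adjusting for it would deal with the main effect of sex, but it would not give the indicator one meaning in grams.

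**The unit comes from a cited definition.** Whether 20 g and 10 g is the correct German definition cannot be judged from the article and is not judged here. Nor can it be assumed that the cited source offers a single value for both sexes.

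**Conclusion.** The point holds for the heavy-drinking-day indicator. As written, its cut is 100 g for men and 40 g for women, a ratio of 2.5, because sex is adjusted for in both the unit and the threshold. With one common unit the same rule would give 1.25. This rests on reading the threshold in standard drinks; taking it as strictly more than five or four drinks gives 2.4. It is a stated rule that works badly, not a detail left for an analysis plan.

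The consequence is limited. One of two derived alcohol measures is affected, for one of several risk factors, in a secondary and exploratory analysis of one arm. The K6 primary outcome, the sample size and the randomised comparison do not depend on it.

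**What to change.** Convert the recorded beverages to grams of alcohol per day, or to one drink unit common to both sexes. Let sex enter only once, in the heavy-day threshold. State that threshold in grams for men and for women, and say whether the cut is inclusive. The authors need to choose and justify the common unit, since the article supplies none. If a wide gap between the sexes is intended, the two gram values and the reason for them should be written down.

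The cost is one change to the text that explains drink equivalents to participants and one change to a derived variable. No further data are needed, because beverages are already to be recorded by type. Trial Status says the study is still in preparation, so the change can be made before participants are taught the unit.
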